**CONTRIBUTION TO THE OBJECTIVES OF THE ACT CONSORTIUM**

**Indicate how this proposal meets the overall objectives of the Consortium under each of the objectives from the front page above (maximum 100 words per objective)**

1. **Improving access.**

This project examines the role of community-based treatment providers in improving access to ACTs, and the feasibility and cost-effectiveness of interventions at the community-level to improve malaria diagnosis, appropriate treatment and referral. The research proposed examines the role of two different types of providers in maximising access to prompt effective treatment at the community level: village-based community drug distributors (an extension of the public health sector) and commercial drug shops and pharmacies (private sector). The project evaluates the impact of introducing confirmatory diagnosis at the community level in increasing the proportion of cases that receive ACT treatment, and in reduced delay in seeking treatment.

1. **Improving drug targeting.**

This project examines the feasibility and cost-effectiveness of using rapid diagnostic tests (RDTs) to improve ACT targeting at the community level. The project will investigate the impact of RDT use on rational drug prescribing and dispensing of ACTs by two key providers of malaria treatment: 1) village-based community drug distributors and 2) commercial drug shops and pharmacies. In addition to impact of diagnostic testing on over-diagnosis and over-prescription; the study will also examine whether diagnostic testing in the private sector results in improved drug targeting through most frequent purchase of the correct drug, in the correct quantity, and patient adherence to the full course of treatment.

**ETHICAL ISSUES**

**Discuss ethical aspects of the proposal.**

*Treatment & referral:*

Patients seeking treatment for fever from a registered drug shop in the intervention areas will be offered a RDT prior to drug purchase. Patients declining a test (and patients seeking treatment at registered drug shops in non-intervention areas) will receive presumptive treatment, in accordance with national guidelines for home-management of malaria (current practice).

Shopkeepers will be trained in taking a fingerprick blood sample, and sterile precautions. Sharps containers will be provided, and collected regularly for correct disposal at the health facility by the research team.

Shopkeepers will be trained on how to recognize and distinguish uncomplicated & severe malaria, supplying unit-dose packaged Coartem® for patients with uncomplicated malaria and the administration of rectal artesunate pre-referral treatment to children with severe and complicated malaria. Cases of severe malaria will be referred immediately to the nearest health unit. In case of a febrile patient with a negative RDT (i.e. non-malaria), those with danger signs and/or axillary temperature >38.5 will also be referred to the nearest health unit. This additional temperature criterion is based on the WHO definition of hyperthermia and is intended to help ensure that patients with severe bacterial infections are seen at a health unit.

To minimise the risk of inadvertent exposure to ACTs during pregnancy, drug sellers will be trained to administer and RDT test, and to refer RDT-positive pregnant women (or women that suspect they may be pregnant) to a health facility for examination by a midwife prior to antimalarial treatment.

*Informed consent:*

Consent will be obtained from drug shop owners to participate in the trial, for randomization of shops to receive RDTs, to keep records on diagnosis and drug sales, and to make these available to the research team. Meetings will be held with the communities in the study areas to describe the purpose of the study, the procedures to be followed, and the risks and benefits of participation.

Patients are free to choose which source of treatment they use, including government health facilities which perform RDT testing, registered drug shops that offer RDT testing and others which use presumptive treatment. Furthermore, it is the patient’s choice which shops they use, and they will be able to choose between outlets that offer diagnostic testing and those that do not, as this service will be openly advertised. Patients seeking treatment for fever from a registered drug shop in the intervention areas will be offered a RDT prior to drug purchase, and have the right to decline the test.

Patients will be recruited on exit from the drug outlet. Individual informed consent will be sought from patients (parents or guardians, in the case of minors) to participate in an exit interview and subsequent follow-up visits at home in order to evaluate the impact of the intervention on malaria treatment. Patients will be informed that participation in the study is completely voluntary and that they may withdraw from the study at any time. Informed consent will also be sought from all informants prior to undertaking any other interviews (focus group discussions, household surveys, etc.).

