### *Secondary endpoints*

- Proportion of patients receiving prompt effective treatment from a commercial drug outlet: % of patients diagnosed with malaria who receive appropriate2 ACT treatment within 24 hours of onset of malaria.
- Acceptability of RDTs: % of patients offered a diagnostic test, % of ACT sales preceded by a test
- Perceptions of ACTs and other antimalarial drugs (amongst community; drug sellers; health staff)
- Perceptions and acceptability of malaria diagnosis using RDTs (amongst community; drug sellers; health staff)
- Willingness to offer and perform RDTs to malaria patients (among drug sellers, health workers)
- Patient adherence to prescription (complete dose taken by day 4)
- Referral: Appropriate treatment of RDT negative patients (lack of antimalarial sale and provision of referral); Timeliness and uptake of referral at a health unit by referred patients.
- Coverage of prompt effective treatment: % of patients with fever who received ACT treatment within 24 hours of onset of malaria, measured through household surveys. For comparison with the WHO/RBM indicator in national and international statistics, coverage in children <5 years will be reported separately from older children and adults.
- Source of treatment: % of patients attending health facility for treatment; % visiting a drug shop
- Equity of diagnosis: % of malaria patients receiving a diagnostic test for malaria, across socio-economic groups.
- Equity of treatment: % of patients, who are diagnosed with malaria, receiving treatment with an ACT, across socio-economic groups.

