Non-malarial fevers: By law, registered class C drug shops are not permitted to stock antibiotics or other “prescription only” medicines. Commercial drug sellers will therefore also be trained to examine and refer febrile patients with fever (axillary temperature >37.0OC and a negative RDT (i.e. non-malaria) to the nearest health facility for examination and treatment by a fully qualified health worker, where appropriate. Any patient with danger signs and/or a temperature >38.5OC and a negative RDT should be referred to the nearest health unit as an urgent case. This additional temperature criterion is based on the WHO definition of hyperthermia and is intended to help ensure that those with severe bacterial infections are seen at a health unit. These patients will also be referred using the emergency referral form, which includes details of symptoms and the use of prior treatment. Shops will keep a dated register for referrals and copy of the referral form with personal identifiers (also at health units).

Shopkeepers will be trained to advise RDT negative patients with fever (axillary temperature ≥ 37.0OC) or other symptoms to seek treatment at the nearest health facility for further evaluation by a fully qualified health worker. A standard referral form will be provided to the patient for this purpose. Where no other symptoms are present, the patient will be advised on tepid sponging, but to return for further assessment at the drug shop or a health facility should the symptoms persist or worsen.

To minimise the risk of inadvertent exposure to ACTs during pregnancy, drug sellers will be trained to administer and RDT test, and to refer RDT-positive pregnant women (or women that suspect they may be pregnant) to a health facility for examination by a midwife prior to antimalarial treatment.

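### The Protocol both refers and sends home an RDT-negative patient who has fever but no other symptom, and the referral endpoint depends on which statement is followed

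*Protocol*

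**What the plan says.** In section (c) of the Protocol, under the referral mechanism for severe malaria and non-malarial fevers, four instructions cover RDT-negative patients.

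- Routine referral, first paragraph: sellers are trained to "examine and refer febrile patients with fever (axillary temperature >37.0OC and a negative RDT (i.e. non-malaria) to the nearest health facility", with a qualifier that leaves some room for judgement.
- Urgent tier, same paragraph: "Any patient with danger signs and/or a temperature >38.5OC and a negative RDT should be referred to the nearest health unit", as an urgent case. An emergency referral form is used.
- Routine referral, second paragraph: shopkeepers are trained to "advise RDT negative patients with fever (axillary temperature ≥ 37.0OC) or other symptoms to seek treatment at the nearest health facility", and the patient receives a standard referral form.
- Home advice, same second paragraph: "Where no other symptoms are present, the patient will be advised on tepid sponging". The patient is told to come back to the shop or go to a facility if symptoms continue or get worse.

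The Ethical issues section (Treatment & referral) describes referral of febrile RDT-negative patients in one sentence: "those with danger signs and/or axillary temperature >38.5 will also be referred to the nearest health unit". It mentions no lower threshold and no standard form.

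The secondary endpoints include a referral endpoint, "Appropriate treatment of RDT negative patients (lack of antimalarial sale and provision of referral", together with timeliness and uptake of referral among referred patients. No temperature or symptom condition is attached.

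**The concern.** In intervention areas, sellers are trained to recommend an antimalarial only after a positive test. The referral section also states that class C drug shops may not by law stock antibiotics. For a patient with a negative test, referral is therefore the Protocol's route to treatment, and drug sellers have to apply it from what they are taught. If the source text gives two actions for one patient, training can follow either.

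There is also a measurement problem. The secondary endpoint treats provision of referral as part of appropriate care after a negative test. If one instruction tells the seller to give home advice, a seller who complies with it fails the endpoint. Timeliness and uptake are measured among referred patients, so their denominator also changes with the statement that sellers follow.

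**Working it through.** The Protocol gives no figure to reproduce here. The check applies each statement, as written, to the same RDT-negative patients. A dash means that the statement does not apply.

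| Patient | First paragraph, above 37.0 | Urgent tier | Second paragraph, 37.0 or above, or other symptoms | Home-advice sentence | Ethical issues |
|---|---|---|---|---|---|
| 36.8 °C, no other symptom | – | – | – | home advice | not listed |
| 37.0 °C, no other symptom | – | – | advice and form | home advice | not listed |
| 37.1, 38.0 or 38.5 °C, no other symptom | refer | – | advice and form | home advice | not listed |
| 37.1, 38.0 or 38.5 °C, other symptoms, no danger sign | refer | – | advice and form | – | not listed |
| 38.6 °C, no other symptom | refer | refer urgently | advice and form | home advice | refer |
| 38.0 °C, danger signs and other symptoms | refer | refer urgently | advice and form | – | refer |

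Reading across:

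1. **Fever alone, above 37.0 and up to 38.5 °C.** Two statements refer and one gives home advice. In the second paragraph fever and other symptoms are joined by *or*, so fever alone is enough for referral. The home-advice sentence then takes the absence of other symptoms as its only condition. This is the contradiction, and it lies within the methods text itself.
2. **Exactly 37.0 °C.** The first paragraph does not refer and the second does. The two thresholds differ at this one reading only.
3. **Fever with other symptoms but no danger sign, above 37.0 and up to 38.5 °C.** Both routine statements refer. Only the ethics section differs, by not listing these patients.
4. **Above 38.5 °C with no other symptom.** The urgent tier and the ethics section agree on referral. Only a literal reading of the home-advice sentence departs from them.
5. **Danger signs.** The methods and the ethics section agree.

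For the endpoint, take the patient at 38.0 °C with fever alone who is sold no antimalarial. A seller who follows either routine statement provides referral and meets the definition. A seller who follows the home-advice sentence does not, although both acted on a Protocol instruction.

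**The case against.** The strongest reply is that the home-advice sentence completes the one before it. The second paragraph first deals with measured fever or other symptoms, and what remains is a client who came for reported fever but has neither at the shop. On that reading nothing conflicts. It is possible but strained. Tepid sponging is a measure against fever, the advice to return presupposes a symptom that may persist, and the phrase about other symptoms repeats the one just set against fever. If this was the intention, the text does not say so. The endpoint mismatch would also remain, because the endpoint as worded covers RDT-negative patients without regard to temperature.

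Other parts of the reply stand.

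- A reader might infer four mutually incompatible referral rules. The text does not support that. In the methods, the criterion of danger signs or more than 38.5 °C is an urgent tier added to routine referral, not a rival to it.
- A reader might take the ethics section to mean that patients below that level are sent home. It omits the routine tier but does not deny it, and it calls the temperature criterion an additional one.
- A reader might infer that the ethics committees were shown a narrower rule. Nothing says they saw that section alone. The referral procedure is part of the same proposal.
- The qualifier in the first paragraph leaves discretion, so that statement is not absolute.

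**Conclusion.** The point holds for a defined group: RDT-negative patients with fever but no other symptom or danger sign. For them the methods text directs both referral and home advice. The incomplete ethics wording and the two forms of the 37.0 °C threshold are secondary.

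The consequence is limited to the clarity of the referral procedure and to the secondary referral endpoint. The primary treatment endpoints rest on blood-slide or RDT result and drug received, and the sample size rests on the slide-based composite. Neither uses the referral rule.

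No number of patients can be attached. It is tempting to start from the 3 × 620 = 1,860 patients planned for the intervention arm and assume 30% to 70% positive, which gives 1,860 × 0.3 = 558 to 1,860 × 0.7 = 1,302 test-negative patients. That range rests on an assumed positivity and on everyone accepting the test, although patients may decline. It also counts all test-negative patients, not those with fever alone, and the documents give no temperature or symptom distribution from which to narrow it.

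The conclusion assumes that the home-advice sentence includes patients with fever, which is its more natural meaning. Training materials and referral forms are not shown and may already settle the matter.

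**What to change.** The sponsor should reconcile the routine statements, the urgent tier and the home-advice sentence in the referral section with each other and with the Ethical issues section, so that there is one referral rule with one form of the threshold. It should say in terms what happens to an RDT-negative patient with fever and no other symptom. The same wording should go into seller training and onto the standard and emergency referral forms.

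The secondary referral endpoint should then be defined by that rule, stating which RDT-negative patients require referral, so that a seller who follows the Protocol is scored as appropriate and the denominator for timeliness and uptake is fixed.

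This review takes no view on which threshold or action is right. The cost is wording in the Protocol and the training material, and notice of the clarified text to the ethics committees. Design and sample size do not change.

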**Submission to ethics committee(s) (specify which committees it will be submitted to)**

Uganda Council for Medicine, Science and Technology, Uganda

Ethics Committee, London School of Hygiene & Tropical Medicine, UK

**OPEN ACCESS AND PUBLIC HEALTH LIAISON GROUP (PHLG).**

**Submitting this proposal means investigators accept**

**a) the commitment to open access to data produced in research funded by the ACT Consortium agreed at the PIs meeting (available on the ACT Consortium Website once ratified by all PIs)**

**b) that as a condition of accepting funds through the ACT Consortium data partly or wholly collected from research funded by the ACT Consortium will be made available to the Public Health Liaison Group within a timescale agreed prospectively by the PI of the project, the Chair of the PHLG and the Secretariat, which will be part of the contract between the ACT Consortium and the institution where the grant will be held.**

**To signify agreement to this**

**Type initials of corresponding PI with date:** [name]

**Type initials of lead PI(s)* with date:** [name]; [name]

1. The proportion of correctly treated malaria cases is based on the “gold standard” of a blood slide read by an experienced research technician. Appropriate treatment is a composite definition including both a) those who a slide-positive who are given a 1st-line antimalarial and b) those who are slide-negative who are not given a 1st-line antimalarial (irrespective of dosing). [↑](#footnote-ref-2)

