**(b) Aim and objectives**

**Aim:** This study aims to examine the feasibility of introducing RDTs into registered drug shops in Uganda to encourage rational drug use in case management of malaria,with a focus on the correct use and adherence to ACTs. Study outcomes will assess drug prescription practices in drug shops and public health services, as well as treatment-seeking behaviour by local communities, including sources of drug treatment, consumer preferences, demand for improved diagnosis, and use of ACTs. The study also examines differences in utilization between households and ability of the approach to improve quality of diagnosis and treatment, especially amongst the poorest members of society.

It is hypothesised that the use of diagnostic testing will reduce over-diagnosis and over-prescription of antimalarial drugs in the private sector. It is further hypothesised that the availability of diagnostic testing in drug shops and confirmation of malaria will increase uptake and sale of ACT combinations (rather than monotherapy or cheaper, less efficacious, antimalarial drug combinations), and may also encourage purchase of the full treatment dose, as well as patient adherence to the full course of ACT treatment.

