### RDTs have recently been introduced into government health facilities in Uganda. Government health staff in the study area will therefore receive additional supportive training to use RDTs and to only provide treatment with Coartem® after a positive result. The study will ensure that public health facilities are well stocked with RDTs, antimalarials and other essential drugs through the government credit supply system. Community sensitization meetings will be carried out to increase awareness of ACTs, reasons for the new treatment policy for malaria, the need for better diagnosis, and importance of adherence to treatment.

| **Private facilities (pharmacies and drug shops)** |
| --- |
| Drug shops randomised to either:  1) Confirmatory diagnosis with RDTs, followed by sale of a commercially-available ACTs only to those who have a positive RDTs  **or**  2) Current practice:  Presumptive clinical diagnosis and treatment of fever |

*Key strengths to the study site*

- - Multiple sampling points within the same district and health system
  - Study design allows comparison between private and public health care providers to assess patient preferences

This allows direct comparison of the effectiveness of treatment, and the cost-effectiveness of improved diagnosis, in a range of different health care providers within the same country.

*Primary endpoints*

- Proportion of patients receiving appropriate treatment from a commercial drug outlet: % of patients diagnosed with malaria who receive appropriate[[1]](#footnote-2) ACT treatment (irrespective of time since onset of treatment).
- Over-prescription: % of patients, who are not parasite-positive, who receive inappropriate ACT treatment from a commercial drug outlet.
- Provider adherence to RDT result: % of patients who receive appropriate treatment, consistent with RDT result
- Cost-effectiveness of RDT compared to presumptive treatment in home management of uncomplicated malaria.

All endpoints will be examined and reported according to age and sex: children aged 0-4y, 5-15y and adults ≥ 16y. For each age group, the proportion of patients receiving appropriate treatment will be compared between shops with RDTs and shops without RDTs, in order to determine whether diagnostic testing reduces overuse of antimalarials in that age group.

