***Evaluation***

*Appropriateness of treatment and/or referral*

Prescription patterns and drug sales in private shops and clinics will be measured through the use of exit interviews, drug sales records and mystery shopper visits. Drug sales records will be adapted to include data on RDT results. Semi-structured exit interviews will be used to ascertain whether diagnostic testing was offered, was accepted by the patient, and type and quantity of drugs sold. Exit interviews will also investigate the patient’s perception of diagnostic testing and their knowledge and understanding of the test result, treatment advice and/or referral. In non-intervention areas, a finger-prick blood sample will be taken to prepare a research blood film to ascertain by microscopy whether the fever was due to malaria. A random sample of patients will also be followed at home after several days to ascertain adherence to treatment (see section below), outcome of the illness and total household expenditure on treatment. Patients will be recruited on exit from the drug outlet and individual informed consent will be sought from patients (parents or guardians, in the case of minors) to participate in an exit interview and any subsequent household visits.

The appropriateness of treatment provided will be evaluated as the proportion of correctly treated malaria cases, based on the “gold standard” of the research blood slide read by an experienced research technician. Appropriate treatment of fever is a composite definition including both a) those who a slide-positive who are given a 1st-line antimalarial and b) those who are slide-negative who are not given a 1st-line antimalarial. Over-prescription will also be assessed as the proportion of children who are not parasite positive who receive inappropriate ACT treatment.

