### *Sample size requirements*

### Sample size requirements for a cluster-randomised trial15 were calculated for the primary endpoint of the proportion of patients receiving appropriate treatment (in line with parasitological status). Appropriate treatment is defined as a composite including both a) those who are slide-positive who purchase an ACT and b) those who are slide-negative who do not purchase an ACT or other antimalarial drug. As the priority for improving treatment in the private sector is to increase the proportion of true cases that purchase and use an ACT (as opposed to antipyretics only, without any antimalarial treatment), we do not include prompt appropriate treatment within 24 hours as the primary endpoint in this work package.

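### The primary composite scores a slide-negative patient sold a non-first-line antimalarial as a success in two places and as a failure in a third

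*Protocol*

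**What the plan says.** Appropriate treatment is a two-part composite judged against the research blood slide. The slide-negative part appears three times in the protocol:

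- Footnote 1 to Primary endpoints: "those who are slide-negative who are not given a 1st-line antimalarial (irrespective of dosing").
- Evaluation, under appropriateness of treatment and/or referral: "those who are slide-negative who are not given a 1st-line antimalarial".
- Sample size requirements: "those who are slide-negative who do not purchase an ACT or other antimalarial drug".

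The third is not a separate outcome. That section says it concerns "the primary endpoint of the proportion of patients receiving appropriate treatment (in line with parasitological status"). The slide-positive part also changes wording: the first two places require a first-line antimalarial, the third "those who are slide-positive who purchase an ACT". That matters only if some ACT on sale is not first-line.

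Other endpoints do not settle the matter. Over-prescription, also a primary endpoint, counts ACT only: "Over-prescription: % of patients, who are not parasite-positive, who receive inappropriate ACT treatment from a commercial drug outlet". The secondary referral endpoint for RDT-negative patients requires that no antimalarial of any kind was sold. No text ranks the definitions.

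**The concern.** The disputed patients are slide-negative and leave the shop with an antimalarial that is not first-line. The protocol expects such products to be on sale. Its second hypothesis is that testing will raise "uptake and sale of ACT combinations (rather than monotherapy or cheaper, less efficacious, antimalarial drug combinations"). Intervention sellers are trained to recommend Coartem only after a positive test, so offering a different antimalarial to a test-negative customer is a foreseeable response.

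The first-line rule credits that substitution as success, and the any-antimalarial rule does not. The first hypothesis in Aim and objectives, and the stated purpose of the age-group comparison under Primary endpoints, concern overuse of antimalarials generally, not of ACT alone. If the rule is chosen after the sales data are known, the primary result is not pre-specified.

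**Working it through.** **The same patient under each rule.** Take a slide-negative patient sold only a non-ACT, non-first-line antimalarial. Footnote 1: no first-line drug given, success. Evaluation: the same, success. Sample size requirements: another antimalarial purchased, failure. The conflict is textual and needs no arithmetic.

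**Reproducing the plan's figure.** Inputs from Sample size requirements: 50% baseline, 75% and 20% targets, 90% power, 95% significance level (read as two-sided alpha 0.05), k = 0.25, m = 61 per cluster. With the cited cluster-trial formula, without its added cluster:

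c = (1.960 + 1.282)² × V / (p0 − p1)², where V = p0(1−p0)/m + p1(1−p1)/m + k²(p0² + p1²)

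- 50% vs 75% (RDT-positive): V = 0.05795, c = 9.74, rounded up to the stated 10.
- 50% vs 20% (RDT-negative): V = 0.02485, c = 2.90.

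The RDT-positive contrast sets the sample size.

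**What the choice of rule does to the effect.** These are assumptions, not document figures: ACT is the first-line drug; the 50%, 75% and 20% rates apply by slide status; slide positivity is π; and a share s0 (control) or s1 (intervention) of slide-negatives is sold only a non-ACT antimalarial.

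- First-line rule: control = 0.50π + 0.50(1−π); intervention = 0.75π + 0.80(1−π).
- Any-antimalarial rule: control = 0.50π + (0.50 − s0)(1−π); intervention = 0.75π + (0.80 − s1)(1−π).

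The effect under the second rule therefore equals the effect under the first plus (1−π)(s0 − s1).

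With π = 0.30 and s0 = 0, power at 10 clusters per arm is Φ(√10 × |p1 − p0| / √V − 1.960):

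| Rule | s1 | Control | Intervention | Effect | Power |
|---|---|---|---|---|---|
| First-line only | any | 50.0% | 78.5% | 28.5 points | about 95% |
| Any antimalarial | 10% | 50.0% | 71.5% | 21.5 points | about 83% |
| Any antimalarial | 20% | 50.0% | 64.5% | 14.5 points | about 54% |
| Any antimalarial | 30% | 50.0% | 57.5% | 7.5 points | about 20% |

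The 30% row is the case where every avoided ACT sale is replaced by another antimalarial (50% − 20% = 30%).

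**Sensitivity to slide positivity.** At s1 = 20%, power under the any-antimalarial rule is about 68% at π = 0.50 (50.0% vs 67.5%) and about 80% at π = 0.70 (50.0% vs 70.5%).

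**Other patterns of sale.** At π = 0.50 with s0 = s1 = 10%, the composite is 45.0% vs 72.5%. That is 27.5 points, the same as the 50.0% vs 77.5% under the first-line rule. With s0 = 20% and s1 = 0 it is 40.0% vs 77.5%, a larger effect of 37.5 points.

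**The case against.** Several stronger readings are tempting, and the case against them is good.

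- *A reader might infer that the two rules could give opposite conclusions.* In the range above the effect shrinks but never changes sign. What can be lost is the demonstration of an effect.
- *A reader might set the shift within one arm against the planned effect.* At π = 0.30, a 20% share moves one arm by 0.70 × 20 = 14 points. Only the difference between arms, s0 − s1, changes the comparison, so equal shares cancel.
- *A reader might conclude that the sample size is undermined.* It is not driven by the disputed rule: 10 clusters come from the RDT-positive contrast, and the RDT-negative contrast needs about 3.
- *A reader might infer that substitution would go unseen, or that it would earn a shop a perfect score.* The composite also depends on slide-positive patients, and the secondary referral endpoint records any antimalarial sale to RDT-negatives. It is secondary, however, and based on the RDT rather than the slide.
- *A reader might call the ACT-only over-prescription endpoint an error.* Its drug scope is the same in both places, so broadening it is optional. The Evaluation section does restrict it to the "proportion of children who are not parasite positive who receive inappropriate ACT treatment", whereas the endpoint list says patients and requires all endpoints by age group, adults included. That is a minor slip.

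The substitution shares are also uncertain. The protocol reports that fewer than 40% of adults and 25% of children visiting a drug shop buy any antimalarial. Those figures describe all clients at baseline and are not a strict ceiling for slide-negatives, but they make the 30% row an extreme, especially for children.

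None of this removes the conflict between the definitions.

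**Conclusion.** The point holds as an inconsistency in the definition of a primary endpoint, and it should be resolved before analysis. It is not merely detail that a statistical analysis plan would supply, because the protocol states the rule and does so in two incompatible ways.

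The consequence is conditional. It is nil if non-ACT sales to slide-negatives are equal in the two arms. The any-antimalarial rule gives a smaller effect if these sales are higher in intervention shops and a larger one if they are higher in control shops. The calculated losses rest on assumed slide positivity and assumed one-sided substitution, since the protocol gives neither. They show that the choice can matter; they do not predict what the trial will find.

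**What to change.** Before analysis, put one definition in footnote 1, the Evaluation section and the sample size section. The sample size section's version is the better fit: a slide-negative patient is appropriately treated only if sold neither an ACT nor any other antimalarial. It matches the aim of reducing antimalarial overuse and agrees with the secondary referral endpoint. Use one term for the slide-positive part as well.

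Three smaller changes follow:

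- Report the first-line-only version as a sensitivity analysis.
- Restate the slide-negative baseline in Sample size requirements as purchase of any antimalarial; it is now given as ACT purchase.
- Replace children with patients in the over-prescription sentence of the Evaluation section.

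The cost is small. Exit interviews already record the type and quantity of drugs sold, so no new data are needed. The planning text needs a short restatement, and appropriate-treatment rates may look lower than under the footnote.
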